### 3.11.5. Quality Control and Quality Assurance

• The clinical study unit must be a clinical pharmacological research centre eligible for clinical studies recognized by the CFDA.

• Research staff should be physicians trained on clinical trials, and they should work under the guidance of senior professionals;

• Clinical wards should be checked to meet the standardized requirements before the trial to ensure well-equipped rescue;

• It is recommended that professional nursing staff administer the drugs to the subjects, and these staff should have a detailed understanding of the use of the drugs and ensure the compliance of the subjects.

• The research center should conduct the study in strict accordance with the study protocol, and truthfully fill in the case reports;

• An independent imaging evaluation committee should be established. The results of imaging examinations (including MRI and CT) of all patients should be confirmed by the independent imaging evaluation committee. All patients with CR, PR, SD and PD efficacy evaluations must first be reviewed by the person in charge of the research unit (PI), and all imaging data for efficacy evaluation (including image films or imaging examination CDs) must be retained and finally confirmed by the independent imaging evaluation committee. The data required by the independent imaging evaluation committee should be the imaging data of each center, and should be provided by local monitors in the form of CDs.

• Monitors should also supervise the the progress of clinical trial following standard operating procedures, and ensure that all data are accurately and completely recorded and reported, all case report forms are entered properly and consistent with the original data, and the study is conducted conforming to the clinical study protocol.

• In case of an SAE, the research units must be notified in time, and when necessary, the study must be temporarily suspended;

• Each research unit participating in the trial should be inspected by the sponsor and the drug administration department, and more importantly, the investigator and relevant personnel should facilitate such supervision and inspection.

# Appendix 1 AJCC/UICC 7th Edition TNM Staging

Nasopharynx (T)

T1 Tumor only in the nasopharynx or invades the oropharynx and/or nasal cavity, and does not invade the parapharyngeal space

T2 Tumor invades the parapharyngeal space

T3 Tumor invades the skull base and/or paranasal sinus

T4 Tumor invades the intracalvarium, cranial nerves, laryngopharynx, eye socket or infratemporal fossa/masticatory muscle space

Regional lymph nodes (N)

N1 Metastasis of unilateral or bilateral retropharyngeal lymph nodes, with the maximum diameter ≤ 6 cm

Metastasis of unilateral cervical lymph nodes, of the maximum diameter ≤ 6 cm and above the supraclavicular fossa

N2 Metastasis of bilateral cervical lymph node, with the maximum diameter ≤ 6 cm and above the supraclavicular fossa

N3a The maximum diameter > 6 cm

N3b Metastasis of supraclavicular lymph nodes

Distant metastasis (M)

M0 No distant metastasis

M1 With Distant metastasis

Overall Staging

Stage 0 Tis N0 M0

Stage I T1 N0 M0

Stage II T1 N1 M0

T2 N0 M0

T2 N1 M0

Stage III T3 N0, N1 M0

T1, T2, T3 N2 M0

Stage IVA T4 N0, N1, N2 M0

Stage IVB Any T N3 M0

Stage IVC Any T Any N M1

# Appendix 2 ECOG PS Scoring

| **Score** | **ECOG performance status** |
| --- | --- |
| 0 | Fully active, able to carry on all pre-disease performance without restriction |
| 1 | Restricted in physically strenuous activity but ambulatory and able to carry out work of a light or sedentary nature, for example, light house work, office work |
| 2 | Ambulatory and capable of all self-care but unable to carry out any work activities; Up and about more than 50% of waking hours |
| 3 | Capable of only limited self-care, confined to bed or chair more than 50% of waking hours |
| 4 | Completely disabled; Cannot carry on any self-care; Totally confined to bed or chair |

# Appendix 3 Flow Chart of the Study

| **Item** | **Within 4 weeks before treatment** | **Within 1 week before treatment** | **Treatment cycle** | | | | | | | | | | |
| --- | --- | --- | --- | --- | --- | --- | --- | --- | --- | --- | --- | --- | --- |
|  |  |  | **Cycle 1** | | | **Cycle 2** | **Cycle 3** | **Cycle 4** | **Cycle 5** | **Cycle 6** | **Odd cycles** | **Even cycles** | **End of treatment/withdrawal** |
|  |  |  | 1 w | 2 w | 3 w |  |  |  |  |  |  |  |  |
| Sign the Informed Consent form | **ⅹ** |  |  |  |  |  |  |  |  |  |  |  |  |
| Treatment history | **ⅹ** |  |  |  |  |  |  |  |  |  |  |  |  |
| Vital signs | **ⅹ** | **ⅹ** |  |  | **ⅹ** | **ⅹ** | * | # | * | # | * | # | **ⅹ** |
| ECOG PS score | **ⅹ** | **ⅹ** |  |  | **ⅹ** | **ⅹ** | * | # | * | # | * | # | **ⅹ** |
| Blood pressure a | **ⅹ** | **ⅹ** | **3** | **3** | **3** | * | * | * | * | * | * | * | **ⅹ** |
| Blood sample b |  | **ⅹ** |  |  | **ⅹ** | **ⅹ** | * | # | * | # | * | # | **ⅹ** |
| Routine blood tests |  | **ⅹ** |  |  | **ⅹ** | **ⅹ** | * | # | * | # | * | # | **ⅹ** |
| Hepatic and renal function, electrolyte |  | **ⅹ** |  |  | **ⅹ** | **ⅹ** | * | # | * | # | * | # | **ⅹ** |
| EB virus (by PCR) |  | **ⅹ** |  |  | **ⅹ** | **ⅹ** | * | # | * | # | * | # | **ⅹ** |
| Nasopharynx + neck CT/MRI c | **ⅹ** |  |  |  |  | **ⅹ** |  | # |  | # |  | # | **ⅹ** |
| Distant metastasis examination d | **ⅹ** |  |  |  |  | **ⅹ** |  | # |  | # |  | # | **ⅹ** |
| Urine routines e |  | **ⅹ** |  |  | **ⅹ** | **ⅹ** | * | # | * | # | * | # | **ⅹ** |
| Fecal routines (OB) |  | **ⅹ** |  |  | **ⅹ** | **ⅹ** | * | # | * | # | * | # | **ⅹ** |
| Coagulation function |  | **ⅹ** |  |  | **ⅹ** | **ⅹ** | * | # | * | # | * | # | **ⅹ** |
| ECG f |  | **ⅹ** |  |  | **ⅹ** | **ⅹ** | * | # | * | # | * | # | **ⅹ** |
| UCG | **ⅹ** |  |  |  |  |  |  |  |  |  |  |  | **ⅹ** |
| Pregnancy test |  | **ⅹ** |  |  |  |  |  |  |  |  |  |  | **ⅹ** |
| Quality of life score |  | **ⅹ** |  |  | **ⅹ** | **ⅹ** | * | # | * | # | * | # | **ⅹ** |
| Adverse events | **ⅹ** | **ⅹ** | **ⅹ** | **ⅹ** | **ⅹ** | **ⅹ** | * | # | * | # | * | # | **ⅹ** |
| Concomitant medication | **ⅹ** | **ⅹ** | **ⅹ** | **ⅹ** | **ⅹ** | **ⅹ** | * | # | * | # | * | # | **ⅹ** |
| Combination Medication | **ⅹ** | **ⅹ** | **ⅹ** | **ⅹ** | **ⅹ** | **ⅹ** | * | # | * | # | * | # | **ⅹ** |

Note: **1) All observation indicators and examination time should not be affected by the duration of drug suspension, and all relevant examinations (including imaging examinations) during each course of treatment should be performed following the flow chart; 2) It is recommended to suspend the drug for 2 to 3 days before puncture or forceps biopsy (if necessary for the patient) as anti-vascular drugs may affect wound healing (because the drug has a half-life period of 9 hours, and 97% of it can be removed from the body after 5 half-life periods), and restore the drug after the wound is healed.**

*: Same as Cycle 1; #: Same as Cycle 2; a: 3 means to measure the blood pressure once every three days; b: Serum VEGF-A/C and VEGFR-2 levels; c: Re-check every two cycles, and follow up every three months after PD/withdrawal; d: Check for hepatic, pulmonary or osseous metastasis by routine chest imaging, liver B-mode ultrasound and bone scanning examinations. If the physician-in-charge considers it appropriate, CT/MRI/PET-CT can be used instead; e: If the urine routines show urine protein of 2+, please perform the 24-hour urine protein quantitative examination and adjust the dose of the drug according to the examination result; f: Supplementary UCG can be performed if there are abnormal ECG findings and the patient has suspected clinical symptoms, or the physician-in-charge considers it necessary.

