| **Subject Eligibility Criteria: Inclusion Criteria** | Patients to be included in this study must meet all of the following inclusion criteria:  1) Patients with histologically proven recurrent and/or metastatic NPC;  Patients with recurrent and/or metastatic NPC shall meet any of the following items: 1. Recurrence after radiotherapy; 2. Metastasis  2) Patients who have failed the platinum-based therapy and received at least first-line platinum-containing chemotherapy;  3) Male or female patients: aged 18-70 y/o;  4) ECOG Performance Status score: 0-2;  5) The estimated survival is ≥ 3 months;  6) Patients not receiving chemotherapy or radiotherapy 4 weeks before the inclusion;  7) With at least one measurable lesion according to the RECIST criteria (the size measured with MRI or spiral CT scan is ≥ 10 mm and the measurable lesion has not received any radiotherapy);  8) Patients whose major organs function well, i.e., to meet the following requirements 1 week before the inclusion:  a. Routine blood test:  i. Hemoglobin > 80 g/L (no blood transfusion within 14 days);  ii. Neutrophil count > 1.5 × 10^9^/L;  iii. Blood platelet count > 80 × 10^9^/L;  b. Biochemical examination:  i. Total bilirubin ≤ 1.5 × ULN (upper limit of normal);  ii. ALT or AST ≤ 2.5 × ULN (upper limit of normal);  iii. Creatinine < 2.0 × ULN, endogenous creatinine clearance rate > 50 ml/min (Cockcroft-Gault Equation);  9) Females of child-bearing age must undergo a pregnancy test (serum or urine) 7 days before the inclusion, with a negative result and a willingness to take reliable contraceptive methods during the trial;  10) Subjects voluntarily participate in the study, sign the Informed Consent form, and are well compliant and cooperative in follow-ups. |

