## 3.4. Criteria for Inclusion, Exclusion and Withdrawal of subjects

### 3.4.1. Inclusion Criteria

1) Patients with histologically proven recurrent and/or metastatic NPC;

Patients with recurrent and/or metastatic NPC shall meet any of the following: 1. Recurrence after radiotherapy; 2. Metastasis

2) Patients who have failed the platinum-based therapy and received at least first-line platinum-containing chemotherapy;

3) Male or female patients: aged 18-70 y/o;

4) ECOG Performance Status score: 0-2;

5) The estimated survival is ≥ 3 months;

6) Patients not receiving chemotherapy or radiotherapy 4 weeks before the inclusion;

7) With at least one measurable lesion according to the RECIST criteria (the size measured with B-mode ultrasound, MRI or spiral CT scan is ≥ 10 mm and the measurable lesion has not received any radiotherapy);

8) Patients whose major organs function well, i.e., to meet the following requirements 1 week before the inclusion:

a. Blood routine examination:

i. Hemoglobin > 80 g/L (no blood transfusion within 14 days);

ii. Neutrophil count > 1.5 × 10^9^/L;

iii. Blood platelet count > 80 × 10^9^/L;

b. Biochemical examination:

i. Total bilirubin ≤ 1.5 × ULN (upper limit of normal);

ii. ALT or AST ≤ 2.5 × ULN (upper limit of normal);

iii. Creatinine < 2.0 times the ULN, endogenous creatinine clearance rate > 50 ml/min (Cockcroft-Gault Equation);

9) Females of child-bearing age must undergo a pregnancy test (serum or urine) 7 days before the inclusion, with a negative result and a willingness to take reliable contraceptive methods during the trial;

10) Subjects voluntarily participate in the study, sign the Informed Consent form, and are well compliant and cooperative in follow-ups.

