### 3.8.1. Screening Stage

**1) Unless otherwise specified, the following screening procedures must be completed within 4 weeks before the study drug treatment starts:**

• Sign the Informed Consent form;

• Collect demographic data: Gender, date of birth, nationality, height, weight, etc.;

• Tumor diagnosis: Date of diagnosis, histological typing, lesion (primary or metastatic lesion), pathological stage TNM, clinical stage;

• Tumor treatment history:

a. Tumor surgery: Date and name of surgery

b. Radiotherapy history: Time and dose of radiotherapy received

c. Chemotherapy history and targeted treatment history: Name of the drug used, dose, medication cycle, start and end time, reason for dressing change (for dressing change due to disease progression, the imaging evidence should be recorded; for changing of therapies due to intolerance, adverse events and severity should be recorded), efficacy and outcome;

• Date of disease progress, relapse or metastasis after the last treatment;

• Complications treatment history: Including the treatment history of diabetes, hypertension, COPD, etc.;

• Blood pressure monitoring: During the screening period, the investigator will monitor the blood pressure of subjects. Before each blood pressure measurement, subjects are required to avoid smoking and coffee for 30 minutes and rest quietly for at least 10 minutes. During the measurement, they are required to be seated and maintain the elbow and the heart at the same level. Each blood pressure measurement is taken ipsilaterally.

• Imaging examination: Head, chest and abdominal CT or MRI. Bone scan is required when bone metastasis is clinically suspected;

(Written Informed Consent form must be obtained before any medical operation specified in the study. But CT/MRI scanning results obtained before signing the Informed Consent form to participate in this trial can be used for tumor evaluation during the screening period as long as they meet the requirements, provided that the date of such CT/MRI scanning must be within 28 days before the treatment)

• UCG: LVEF will be observed carefully; (Results of ECG examinations performed within 28 days before the signature of the Informed Consent form are acceptable)

• Concomitant medication and treatment: Concomitant medication and treatment within 28 days before enrollment and during the study period will be recorded.

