## 3.9. Efficacy Evaluation

The efficacy is determined in strict accordance with the RECIST 1.1 criteria.

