### 3.9.1. Measuring Method

For both pre-treatment baseline measurement and efficacy evaluation, the same techniques and methods should be used to evaluate the lesion, and such measuring methods should be easily repeatable and enable easy data storage, such as CT and MRI.

Contrast-enhanced CT is the preferred method to evaluate tumors. If the patient cannot undergo contrast-enhanced CT, MRI should be performed. For the head, chest, abdomen and pelvis, CT and MRI scanning should be performed with 10 mm section thickness or thinner, and spiral CT scanning should be performed continuously with 5 mm section thickness.

For superficial lesions that are clinically measurable (e.g., skin nodules and palpable lymph nodes), color images containing a scale to indicate the size of lesions are recommended for the estimation of the lesion size.

Ultrasound should not be used to measure tumor lesions that are clinically difficult to measure (e.g., visceral lesions) in overall response evaluation. Ultrasonography can be used as an optional method for clinical evaluation of superficial palpable lymph nodes, subcutaneous nodules and thyroid nodules. Ultrasonography can also help to confirm the complete disappearance of superficial lesions that are usually evaluated by clinical examination.

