### 3.9.2. Record Tumor Measurement Data

Target lesions should include all the organs involved, with a maximum of 5 target lesions in each organ, and the total number of all target lesions should not exceed 10. They should be measured and recorded at baseline and at the time points specified. Target lesions should be selected based on the size (lesions with the largest diameter) and suitability for repeated accurate measurability (with imaging technique or clinical methods). A primary lesion should be classified as a target lesion only if it can be accurately measured.

The longest diameter of each target lesion will be recorded. The sum of the longest diameters of all target lesions will be calculated and recorded. During the treatment, the objective response of tumors in measurable dimensions will be further clarified by referring to the sum of the longest diameters at baseline.

All non-measurable lesions and other measurable lesions not selected as target lesions should be identified as non-target lesions, and should also be recorded at baseline. Measured data of such lesions are not required in the study, but their presence and disappearance should be tracked throughout the study period.

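### The imaging rules behind the primary ORR conflict: Appendix 3 defaults to liver ultrasound and criterion 7 of 3.4.1 accepts ultrasound at any site, against the CT/MRI rules of 3.8.1, 3.8.2 and 3.9.1

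*Protocol*

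**What the plan says.** **Body text.** Section 3.8.1 lists for screening: "Imaging examination: Head, chest and abdominal CT or MRI". Section 3.8.2 has target lesions re-examined under baseline conditions, including slice thickness and contrast use. Section 3.9.1 asks for the same technique at baseline and at evaluation, and prefers contrast-enhanced CT, with MRI where that is not possible. It adds: "Ultrasound should not be used to measure tumor lesions that are clinically difficult to measure (e.g., visceral lesions"), in the context of overall response evaluation. It keeps ultrasound as an option for superficial palpable nodes, subcutaneous nodules and thyroid nodules.

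**Flow chart.** Appendix 3 has two imaging rows, both due at baseline, at cycle 2 and later even cycles, and at end of treatment. One is CT/MRI of nasopharynx and neck. The other is the distant metastasis examination, defined in note d: "Check for hepatic, pulmonary or osseous metastasis by routine chest imaging, liver B-mode ultrasound and bone scanning examinations". The note then allows CT, MRI or PET-CT instead if the physician in charge thinks it appropriate. Note 1 says examinations, including imaging, are to follow the flow chart.

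**Eligibility.** Criterion 7 in 3.4.1 defines a measurable lesion by "the size measured with B-mode ultrasound, MRI or spiral CT scan is ≥ 10 mm", with no limit on site. The same criterion in the synopsis reads "the size measured with MRI or spiral CT scan is ≥ 10 mm".

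**The concern.** A site can comply with the flow chart and still breach the body text. Metastatic disease is an entry route, so liver and lung lesions can be target lesions, and no flow-chart row other than the distant metastasis row images those organs. A patient could have abdominal CT at screening under 3.8.1 and liver ultrasound at cycle 2 under note d, leaving no valid change from baseline for that lesion. A patient could also qualify on a liver lesion that reaches 10 mm on ultrasound, although 3.9.1 will not accept ultrasound for judging its response.

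The result would be an unassessable or misclassified patient in the primary endpoint. The direction is not predictable. A response read from ultrasound could inflate ORR; a patient without usable scans who stays in the full analysis set could lower it. The choice of method also affects detection of new liver or lung lesions, which 3.9.3.2 counts as PFS events.

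**Working it through.** **1. The passages side by side**

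| Question | Body text | Flow chart or other text |
|---|---|---|
| Liver imaging at screening | Abdominal CT or MRI (3.8.1) | Ultrasound by default; CT/MRI/PET-CT discretionary (Appendix 3, note d) |
| Lung imaging at screening | Chest CT or MRI (3.8.1) | Routine chest imaging by default; CT/MRI/PET-CT discretionary (note d) |
| Liver target lesion at follow-up | Same conditions and method as baseline (3.8.2, 3.9.1); no ultrasound for visceral lesions (3.9.1) | Ultrasound by default at every even cycle (note d) |
| Neck disease | CT or MRI | CT/MRI row; no conflict |
| Ultrasound for the qualifying lesion | Accepted at any site (3.4.1, criterion 7) | Not listed (synopsis, criterion 7) |

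The liver conflict is explicit. The lung conflict rests on one inference: note d offers CT as a replacement for routine chest imaging, so routine chest imaging must mean something other than CT.

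**2. The design figure.** Section 3.3 gives a null ORR of 24.2%, an alternative of 39.2%, one-sided alpha 0.05, power 0.80, 31 patients in stage 1 with stopping at 7 or fewer responders, and 64 patients after 10% drop-out. For final size n and final cut-off r,

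P(declare active | p) = Σ from x = 8 to 31 of P(X1 = x) × P(X2 > r − x), with X1 ~ Bin(31, p) and X2 ~ Bin(n − 31, p).

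An exact search gives the minimax design n = 58, r = 19, with alpha 0.0495 and power 0.8002. Then 58 × 1.10 = 63.8, rounded up to 64. The protocol's figure reproduces and is unaffected by this point. It does not print 58 or 19; both are reconstructed.

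**3. What misclassification could do.** One patient is 1/58 = 1.7 points of ORR. The documents give no misclassification rate, so the shifts below are assumptions, applied equally in both stages under the 7/31, 19/58 rule.

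| Assumed shift in observed ORR | About how many of 58 | Type I error if the null ORR reads high | Power if the alternative ORR reads low |
|---|---|---|---|
| 0 | 0 | 0.050 | 0.800 |
| 2 points | 0.02 × 58 = 1.2 | 0.099 | 0.703 |
| 5 points | 0.05 × 58 = 2.9 | 0.222 | 0.524 |

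These figures show how sensitive the design is to a net error of one to three patients. They do not estimate what note d would cause.

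**The case against.** The strongest reply is that the body text already forbids the harmful sequence: 3.8.2 and 3.9.1 both require the baseline method at follow-up. Note d is worded as a search for metastases, not as a rule for measuring target lesions, and note 1 is mainly about timing. Neck disease has its own CT/MRI row. Section 3.11.5 also has an independent imaging committee confirm every response category.

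Much of this stands as description, but it does not remove the conflict. No other row schedules CT or MRI of the liver or lungs, and note 1 directs imaging to the flow chart, so a site scheduling from it has no prompt to repeat the screening CT. The committee can correct a reading but cannot read a scan that was never taken.

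A reader might go further in four ways that the documents do not support.

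- **That 3.9.1 bars ultrasound outright.** It does not; superficial lesions are allowed. The fault in criterion 7 is the missing site limit and the mismatch with the synopsis.
- **That the target-lesion rules depart from the named standard.** Section 3.9 says "The efficacy is determined in strict accordance with the RECIST 1.1 criteria", and 3.9.2 sets lesion numbers ("with a maximum of 5 target lesions in each organ, and the total number of all target lesions should not exceed 10") and the diameter ("The longest diameter of each target lesion will be recorded"). The protocol does not reproduce the RECIST 1.1 limits or any nodal rule, so a mismatch cannot be shown from it. A dispute over whether a shrunken node is PR or CR would in any case leave ORR unchanged, since 3.9.3.1 counts both.
- **That measurement decides between 20 and 22 responders of 58.** That gap separates the reconstructed one-sided rule (20 or more) from a two-sided 95% Clopper-Pearson lower limit above 24.2% (first met at 22). It is a question of test sidedness, not imaging.
- **That response must be confirmed at the next scheduled scan.** This would redefine the endpoint, and nothing in the imaging conflict calls for it.

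**Conclusion.** The point holds as an internal contradiction about how visceral disease is imaged for the primary endpoint, and it can be shown from the protocol alone. Note d conflicts directly with 3.8.1 on chest and abdominal imaging. It conflicts with 3.8.2 and 3.9.1 wherever a liver or lung lesion has to be followed for response. Criterion 7 differs between the synopsis and 3.4.1.

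The effect on ORR is not quantified. It depends on how many patients have liver or lung target lesions and how many sites follow note d literally, and the documents give neither. The two firm figures are 1.7 points of ORR per reclassified patient, on 58 evaluable, and an unchanged sample size. The type I error and power figures rest on assumed shifts.

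The same-method rule and central confirmation limit the damage, so this is a correction to make rather than a defect that invalidates the design. It is best made before patients are scanned, because missing CT or MRI cannot be recovered later.

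**What to change.** - **Appendix 3, note d:** state that patients with target or known lesions in the chest or abdomen have CT or MRI of those regions at baseline and every two cycles, in the same modality as baseline. This brings the note into line with 3.8.1, 3.8.2 and 3.9.1.
- **Section 3.4.1, criterion 7:** delete B-mode ultrasound to match the synopsis, or limit it to the superficial lesions for which 3.9.1 allows it and amend the synopsis to agree. Either reconciles the text.

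**Cost.** This is a wording amendment. In practice some routine chest imaging and liver ultrasound is replaced by CT or MRI that the body text already calls for. Removing ultrasound from criterion 7 could exclude a few patients whose only qualifying lesion was sized that way; the site-limited alternative keeps those with superficial lesions. The sample size and the stage 1 rule do not change.
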